### Dietary assessment

A 7-day diet diary will be used to measure energy and nutrient intakes and they will be calculated using NutriSurvey 2007 (EBISpro, Germany) nutrient analysis software, modified for Sri Lankan food items and recipes.

### Compliance calculation

Subjects are asked to return any remaining drugs, and their compliance will be evaluated by using the formula:$$ \mathrm{Compliance}\left(\%\right)=\frac{\mathrm{Distributed}\ \mathrm{capsules}\hbox{-} \mathrm{remainining}\ \mathrm{capsules}}{\mathrm{Distributed}\ \mathrm{capsules}}\times 100 $$

### Data protection and confidentiality

Confidentiality will be maintained by giving all volunteers a unique identification code. Names will not be used in any reports or publications. Data will be kept for a maximum of 5 years. The files which match the personal details of the participants with their individual identification code will be held separately in a locked filing cabinet within the Department of Applied Nutrition and will be accessible only to the study investigators.

### Statistical analysis

SPSS version 16 (SPSS Inc., Chicago, IL, USA) will be used for data analysis. For categorical data, Pearson’s chi-squared test will be used to verify the association in the treatment and placebo groups. For binary and continuous outcomes, logistic and linear regression models will be used, respectively. Statistical analysis will be performed by descriptive analysis, with numerical variables expressed as the mean and standard deviation (SD) or median and interquartile range. The Kolmogorov-Smirnov test will be used to test the normality of the sample distribution. The Student *t* test will be used in cases with a normal distribution to compare means between the two groups. The Wilcoxon test will be used in cases with a non-normal distribution. *P* values <0.05 will indicate a significant association in all of the statistical tests used.

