### Randomization and blinding

After the screening phase, subjects will be stratified according to age, gender and BMI and randomly assigned to one of two groups of 40 subjects each into the test and placebo. Assignment to either group will be performed by a computer-generated 1:1 randomization. The study treatments are double blinded to both investigator and subject. The supplements and placebo will be produced by Astron Lanka Limited, Ratmalana, Sri Lanka. They will be responsible for the labelling and packaging of the Zn capsule and placebo with code numbers.

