### Interventions

The study will be conducted for 3 months. The visits and the evaluations will be as follows: screening (visit 0), baseline (visit 1) and 3 month (visit 2). The treatment drug is a capsule containing elemental zinc 20 mg as the active ingredient (as zinc sulphate). The supplemented Zn dose was set based on a previous study published in the literature [14]. The placebo capsule will contain lactose monohydrate. The placebo will be manufactured to have a similar appearance, shape, weight, taste and colour as the Zn capsule. The subjects will receive either one capsule of Zn or an identical placebo daily, taken after dinner for a period of 3 months. Figure 1 illustrates the schedule of the study.

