### Measurements

The primary endpoint is weight reduction among obese adults. Body weight will be measured using a calibrated electronic floor scale (SECA 815 by SECA GmbH & Co. KG, Hamburg, Germany) to the nearest 0.1 kg. Height will be measured to the nearest 0.1 cm using an upright plastic portable stadiometer (IP0955, Invicta Plastics, Leicester, UK). BMI will be calculated as weight (in kilograms) divided by the square of height (in metres). Waist circumference will be measured with a non-elastic tape (SECA 203 by SECA GmbH & Co. KG, Hamburg, Germany) at a point midway between the lower border of the rib cage and the iliac crest at the end of normal expiration. Similarly, the hip circumference also will be measured at the widest part of the buttocks at the intertrochanteric level to the nearest 0.1 cm. All anthropometric measures will be taken by trained research assistants using standard equipment according to the standard guidelines [17]. In addition, glycaemic status (fasting blood glucose), lipid parameters (total cholesterol, triglyceride levels, HDL cholesterol, LDL cholesterol) and blood pressure will be measured. Glucose in the plasma will be determined by the glucose oxidase/peroxidase (GOD-Perid) method using commercially available kits (ProDia International, USA) and a chemistry analyser (Erba Chem-7, UK). Total cholesterol, triglyceride levels and HDL cholesterol (HDL-C) will be measured with enzymatic colorimetric assays using commercially available kits (ProDia International, USA) and an Erba Chem-7 chemistry analyser (Erba Molecular, Cambridgeshire, UK). LDL cholesterol (LDL C) will be estimated based on the Friedewald equation [18]. Systolic (SBP) and diastolic blood pressure (DBP) will be measured after at least a 10-min rest with Omron IA2 digital blood pressure monitors (Omron Healthcare, Singapore).

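### Linear regression and an unadjusted t or Wilcoxon test are both assigned to the same continuous outcomes; a single baseline-adjusted model would be a free improvement

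*Protocol article*

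**What the plan says.** The Measurements section sets the endpoint: "The primary endpoint is weight reduction among obese adults". The Interventions section lists evaluations at screening, baseline and month 3, so each subject's baseline value can be used. Under Randomization and blinding, "subjects will be stratified according to age, gender and BMI and randomly assigned to one of two groups of 40 subjects each".

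The Statistical analysis section then gives two instructions that both cover body weight and every continuous secondary variable:

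- "For binary and continuous outcomes, logistic and linear regression models will be used, respectively".
- A Student t test "in cases with a normal distribution to compare means between the two groups"; otherwise the Wilcoxon "test will be used in cases with a non-normal distribution". The switch is set by a normality test: "The Kolmogorov-Smirnov test will be used to test the normality of the sample distribution".

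One threshold applies throughout: P "values <0.05 will indicate a significant association in all of the statistical tests used". The section does not rank the two routes. It does not say whether the means compared are month-3 values or changes, and it mentions neither baseline values nor the stratification factors.

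**The concern.** Two methods stand side by side for one primary endpoint, each with the same 0.05 threshold. If they give different answers, the text does not say which one is the trial's result.

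The between-group test that is spelled out is unadjusted, while the listed regression could carry the baseline value at no cost. Two things are at stake: precision, which matters mainly for the secondary outcomes, and the freedom to choose between listed tests once the data are seen.

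**Working it through.** The plan has no figure of its own to reproduce on this point. Its 35 per arm (Sample size section) comes without a difference, SD or power.

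**Inputs.** From the article: 35 per arm, 1:1 allocation, threshold 0.05. Assumed, because the article gives none of them: two-sided testing; 80% power; weight SD 12 kg; equal variance at both visits; baseline to month-3 correlation r of 0.90-0.98 for weight and 0.5-0.7 for glucose, lipids and blood pressure.

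**Variance per subject** (σ = SD at one visit):

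- month-3 value: σ²
- change: 2σ²(1 − r)
- ANCOVA: σ²(1 − r²)

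So ANCOVA/month-3 = 1 − r², and ANCOVA/change = (1 − r²)/[2(1 − r)] = (1 + r)/2.

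| r | ANCOVA/month-3 | ANCOVA/change |
|---|---|---|
| 0.50 | 0.75 | 0.75 |
| 0.70 | 0.51 | 0.85 |
| 0.90 | 0.19 | 0.95 |
| 0.95 | 0.0975 | 0.975 |
| 0.98 | 0.0396 | 0.99 |

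For weight (r = 0.90-0.98), ANCOVA removes 1-5% of the variance of a change score and 81-96% of that of a month-3 comparison. For the secondary outcomes (r = 0.5-0.7) it removes 15-25% and 25-49%. Put as sample size, 35 per arm under ANCOVA does the work of 35/0.85 = 41 to 35/0.75 = 47 per arm under change scores.

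**Detectable difference in weight.** Multiplier: (1.96 + 0.84) × √(2/35) = 0.670. At r = 0.95:

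- month-3: 0.670 × 12 = 8.04 kg
- change: SD = 12 × √0.10 = 3.79, giving 2.54 kg
- ANCOVA: SD = 12 × √0.0975 = 3.75, giving 2.51 kg

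| r | Month-3 t test | Change t test | ANCOVA | Power for 2 kg (same order) |
|---|---|---|---|---|
| 0.90 | 8.04 kg | 3.59 kg | 3.50 kg | 10%, 34%, 36% |
| 0.95 | 8.04 kg | 2.54 kg | 2.51 kg | 10%, 60%, 61% |
| 0.98 | 8.04 kg | 1.61 kg | 1.60 kg | 10%, 94%, 94% |

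With SD 8 kg and r = 0.95 the three differences are 5.36, 1.69 and 1.67 kg; with SD 15 kg they are 10.05, 3.18 and 3.14 kg. The pattern does not depend on the SD.

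**Type I error if the smaller p value is reported** (10,000 simulated trials per r, 35 per arm, no treatment effect):

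| r | Change t or ANCOVA | Month-3 t or ANCOVA | Any of the three |
|---|---|---|---|
| 0.90 | 6.1% | 8.9% | 10.1% |
| 0.95 | 5.9% | 9.7% | 10.3% |
| 0.98 | 5.7% | 9.3% | 9.9% |

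Each test alone stayed between 4.6% and 5.3%.

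**The case against.** A reader might infer that the plan ignores baseline weight and so throws away most of its precision. The article does not support this. The endpoint is a weight reduction, and a t test on reductions uses baseline by subtraction. The regression covariates are unstated, not excluded. Nowhere does the article say that raw month-3 weights will be compared, and every alarming figure (8.04 kg detectable, 10% power, 9-10% type I error) needs that reading. On the natural reading, a change t test is valid in a 1:1 randomised trial and nearly as efficient as ANCOVA for weight.

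A regression on arm alone is the equal-variance t test under another name, with the same p value. The two routes therefore compete only if the regression carries covariates. That limits the multiplicity cost to about 6% on the change reading. The choice between t and Wilcoxon is a stated conditional rule, so it is not counted above as a free choice.

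A reader might also infer that naming logistic regression means weight loss will be dichotomised. The sentence is a generic pairing of model to outcome type and supports no such inference.

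Lastly, an article may leave covariates and the choice of lead model to a full protocol or SAP. That is fair, and the point does not rest on that silence. What stands is that the published text itself commits to two routes for the same outcomes, and that the between-group test it spells out is unadjusted where a better one is available from the same data.

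**Conclusion.** The point holds as a free improvement, not as an error that invalidates the trial. Two routes are stated for the same continuous outcomes, without a primary one and without stated baseline adjustment.

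For the primary endpoint read as change, the precision gain from ANCOVA is slight, and the benefit lies in removing the choice between tests. For the secondary outcomes the gain is worth having whether changes or final values would have been compared. Fixing the model also rules out a month-3 comparison, the one reading under which the primary analysis would lose most of its precision.

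The sizes rest on the assumed correlations and, for kilograms and power, on the assumed SD. The type I error figures were simulated for weight-like correlations only.

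**What to change.** State one primary analysis: linear regression of month-3 body weight (kg) on treatment arm and baseline weight, with age, gender and BMI entered as used for stratification. Report the adjusted mean difference with its 95% confidence interval. Use the same model for each secondary variable with its own baseline value. Keep the t and Wilcoxon tests as sensitivity analyses that do not decide the result.

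The cost is a change of wording. Linear regression is already listed, the planned software runs it, and no extra measurement is needed. The Trial status section places the trial in recruitment, so the choice can be fixed before outcome data are examined.

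If a full protocol or SAP already names this model, aligning the published text with it is enough.

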### Sample size

The minimum estimated sample size was 35 for each study arm, and a 15 % dropout rate was calculated. Finally, 40 subjects were recruited for each group.

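### A normality pre-test on the trial data chooses between the t test and Wilcoxon, and regression is named alongside without ranking, so the primary effect measure is not fixed

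*Protocol article*

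**What the plan says.** Four statements in the Statistical analysis section of the protocol article bear on continuous outcomes:

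- Models: "For binary and continuous outcomes, logistic and linear regression models will be used, respectively".
- Gate: "The Kolmogorov-Smirnov test will be used to test the normality of the sample distribution".
- Branch if normal: the Student t "test will be used in cases with a normal distribution to compare means between the two groups".
- Branch if not normal: "The Wilcoxon test will be used in cases with a non-normal distribution".

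One threshold serves every test: P "values <0.05 will indicate a significant association in all of the statistical tests used". The Measurements section defines the main outcome: "The primary endpoint is weight reduction among obese adults". That outcome is continuous, and nothing takes it out of the gated rule.

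The article does not say which Kolmogorov-Smirnov variant is meant, at what level the gate operates, whether it is applied to final values or changes, or whether it is applied per arm or pooled. It also does not rank the regression against the gated pair of tests.

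**The concern.** The t test and the Wilcoxon test do not answer the same question. The first concerns a difference in means and comes with an estimate in kg. The second concerns a shift in ranks and, as described, comes with no estimate in kg. Under the stated rule the trial's own data decide which question is asked of the primary outcome. The regression model is a third route with no stated place in the order.

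This is not a detail left to a later analysis plan. The rule is written down, and it is the rule that is poorly fixed. At stake is whether the primary effect measure is known before unblinding, and whether two analysts following the same text would report the same primary result.

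**Working it through.** **Inputs**

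- From the article: two parallel arms (Randomization and blinding); 35 per arm as the minimum ("The minimum estimated sample size was 35 for each study arm", Sample size); threshold 0.05. The 35 cannot itself be re-derived, because no effect size, SD or power is given; it is used here only as the analysed number.
- Assumed: two-sided tests, gate level 0.05, rank-sum form of Wilcoxon, and illustrative distributions. The article gives no SD, skewness or baseline correlation for any outcome.

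**1. Does the branch depend on the Kolmogorov-Smirnov variant?**

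With mean and SD estimated from the sample, the statistic is D = max|F_n(x) − Φ((x − mean)/SD)|. At n = 35 the 5% critical value is about 0.148 with the Lilliefors correction and about 0.22 to 0.23 without it. Rejection rates in one sample of 35:

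| Distribution | Skewness | Uncorrected | Lilliefors |
|---|---|---|---|
| Normal | 0 | about 0% | 5% |
| Log-normal, log SD 0.25 | 0.8 | 0.2% | 19% |
| Log-normal, log SD 0.4 | 1.3 | 1.6% | 40% |
| Log-normal, log SD 0.5 | 1.75 | 4 to 5% | 54 to 55% |
| Log-normal, log SD 0.6 | 2.3 | 9% | 69% |
| Log-normal, log SD 1.0 | 6.2 | 51% | 97% |

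The same data can therefore go to different tests according to the procedure run.

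**2. Does the branch vary by chance, and does it matter?**

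Take 35 per arm and send a trial to Wilcoxon if either arm fails a Lilliefors gate. Then 9.7% of trials with truly normal data go to Wilcoxon, and 62% at skewness 1.3. For a shift of 0.68 SD, the t test and Wilcoxon disagree on significance in 5% of trials (normal), 10% (skewness 1.3) and 15% (skewness 2.3).

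**3. Type I error**

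Over the distributions tried and both gate variants, the two-stage rule rejects a true null in 0.047 to 0.056 of trials. The t test alone gives 0.044 to 0.050 and Wilcoxon alone 0.047 to 0.052.

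**4. Power**

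Example: log-normal outcome, log SD 0.5, a 25% reduction, 35 per arm.

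- Log-scale effect: −ln(0.75) = 0.288. Standardised: 0.288/0.5 = 0.575. Noncentrality: 0.575 × √(35/2) = 2.41. Power about 66%.
- Raw-scale t test, by simulation: 61 to 62%. Wilcoxon: 63 to 64%.
- The gated rule itself, by simulation: 62 to 65%, depending on variant. The gate thus costs about 1 to 4 points against the log-scale analysis.
- Adjusted for baseline with correlation 0.7: residual SD 0.5 × √(1 − 0.49) = 0.357; standardised effect 0.288/0.357 = 0.806; noncentrality 3.37; power about 91% (90% by simulation).

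The last comparison takes the gated tests as applied to final values. If they were applied to log-scale changes, the SD would be 0.5 × √(2 × (1 − 0.7)) = 0.387, the noncentrality 3.11 and power about 87%, so subtraction would recover most of the gain at this correlation. The article does not say which quantity is tested.

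**The case against.** The best defence is that the rule does little inferential damage. Type I error stays close to nominal, and in the triglyceride-like example the gated rule comes within a few points of the log-scale analysis. This stands, and it limits the point to the choice of effect measure and to efficiency.

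It is also fair to say that regression is already named, so a baseline-adjusted analysis may be intended, with covariates left to a fuller document. That is a reason not to criticise missing covariates. It does not rescue the text, because an unranked third method makes the primary analysis less determinate.

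Some stronger inferences should be resisted:

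- A reader might conclude that the gate cannot detect skewness, or that triglycerides will usually pass as normal. That holds only for the uncorrected test, or in part for mild to moderate skewness. With Lilliefors and log SD 0.5, about 77 to 80% of trials go to Wilcoxon. The article names no variant and speaks of normality, not skewness.
- A reader might set 62% beside about 90% power and blame the gate. Nearly all of that gap comes from baseline adjustment.
- A reader might find the word Wilcoxon ambiguous between rank-sum and signed-rank. The preceding sentence refers to comparing two groups and the design is parallel, so rank-sum is the natural reading.

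**Conclusion.** The point holds in this form: the article lets a pre-test on trial data select the comparison for every continuous outcome, the primary included, and names regression without ranking it, so the primary effect measure is not fixed in advance. The choice of branch is sensitive to an unstated variant (about 5% against 54% rejection at n = 35 for log SD 0.5) and to chance.

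Type I error is not materially inflated, and the gate's own power cost is about 1 to 4 points in the example. The larger potential loss is the missing baseline adjustment: about 62 to 66% against about 90%, if the correlation is 0.7 and final values are compared, and much less if changes are compared. These figures rest on assumed distributions for a triglyceride-like outcome. The article supplies nothing from which to size the loss for weight. The problem should be corrected, but it does not invalidate the trial.

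**What to change.** 1. Delete the Kolmogorov-Smirnov gate and the conditional choice of test.
2. Name the linear regression already listed as the single analysis of weight and the other continuous outcomes, adjusted for the baseline value and the stratification factors (age, gender, BMI), with the adjusted mean difference as the effect measure (in kg for weight).
3. Check the model's residuals, without letting that check replace the primary result.
4. Report a rank-sum analysis, or a log-scale one (for example for triglycerides), only as a pre-specified sensitivity analysis that cannot take the place of the primary result.

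The cost is a change of analysis wording. Baseline weight and the stratification factors are already recorded, the sample size is untouched, and the article reports the trial as still recruiting.

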## Discussion

The level of obesity has reached epidemic proportions in many countries. Several non-communicable diseases such as diabetes, metabolic syndrome, ischaemic heart diseases and certain cancers are strongly associated with obesity. Obesity is a major health burden in south Asian countries including Sri Lanka [3]. Only a very limited number of clinical trials have been conducted in Sri Lanka, although the country is experiencing several health burdens [2, 4, 5]. Experiments on low-cost and effective treatment methods for major health disease in Sri Lanka are greatly needed.

In parallel to the problems of obesity and non-communicable diseases (NCDs), south Asian countries are facing malnutrition and micronutrient deficiencies. A systematic review and meta-analysis showed satisfactory effects of Zn supplementation on diabetes and other metabolic markers, especially studies conducted in developing countries [19]. Hashemipour et al. showed significant body weight reduction and metabolic improvement in a group of pre-pubertal obese children in Iran [11]. However, there is a scarcity of published data on zinc supplementation on obese adults from developing countries where marginal deficiencies are possible.

The proposed study, as far as we are aware, will be the only study of its type to be conducted in Sri Lanka and one of the few studies conducted elsewhere in the world. The findings will be of major importance to clinical practice for the management of obesity using nutritional supplements and to the general public, who will learn about the health impact of taking Zn supplements to lose weight and thus avoid some chronic diseases. The results will also assess mineral deficiencies in people who are obese and are at risk of developing obesity-related diseases. Because of the fundamental nature of the work proposed in this project, the findings are likely to be of significance to a wide range of users such as hospital health care teams and ministries of health who conduct supplementation and fortification programmes to improve the health status of the general public.

### Strengths and weaknesses

The first advantage is that randomized, double-blind placebo controlled trials represent the highest level of research evidence. Second, there are no reported adverse effects of a dose of 20 mg/d of zinc supplementation on otherwise healthy adults. Previous studies on supplementation with zinc (20 mg/d) did not show any adverse effects [11]. We expect a high level of patient compliance in this study. Third, the measurement of metabolic parameters such as plasma lipids, glucose and blood pressure along with anthropometric changes will provide a complete picture of the effect of zinc supplementation on obesity and associated risk factors. However, we do not have the funding or the technical facilities to measure serum zinc values, which may hinder the ability to interpret results related to patients’ zinc status.

### Trial status

This trial is in the recruitment stage.

## Abbreviations

DBP: Diastolic blood pressure
SBP: Systolic blood pressure
SLCTR: Sri Lanka Clinical Trials Registry
HDL-C: High-density lipoprotein cholesterol
LDL-C: Low-density lipoprotein cholesterol
SD: Standard deviation
NCD: Non-communicable disease
